## Data monitoring

6.

The DMC will include the head of the research institution, clinical inspector, and statistician. The DMC will conduct timely data verification according to the established verification plan. Data verification problems will be posed online and addressed by the investigator or their authorized CRC. The DMC will audit the implementation of the trial-related documents, trial data, and trial protocol, as planned, and send audit results to the Clinical Trial Center of Qingdao University and the Medical Ethics Committee. The audit may occur at any time during or after the trial. The investigator will allow the clinical inspector access to all relevant documents.

## Statistical methods

7.

We plan to include data from all the participants assigned to randomized grouping, regardless of intervention, in a intention-to-treat analysis. SPSS version 25.0 will be used to analyze data. The Shapiro–Wilk test will be used to assess normality of continuous variables. Normal data will be described as means ± standard deviations, and otherwise as medians and interquartile ranges. Demographic and intraoperative data will be compared by independent samples *t*-tests, Mann–Whitney U test, chi-square test, Yates’ chi-square test, or Fisher’s exact probability test, as appropriate. The primary study outcome (rebound pain) is dichotomous, and the relative risk (RR) and 95% confidence interval (CI) will be calculated using the modified Poisson regression model for the esketamine and placebo groups. We plan to evaluate three modified Poisson regression models: model 1 will be unadjusted; model 2 will be adjusted for gender, age, BMI, ASA grade, complications, long-term analgesics use, and baseline pain score; model 3 will be adjusted for tourniquet use time, operation time, steroid use (yes/no) and analgesic and sedative doses during the operation. We plan to conduct a sensitivity analysis on the primary outcome. The effects of the intention-to-treat set and the per-protocol set on the consistency of the primary outcome will be compared. The per-protocol set will be whether the participant has completed all main baseline variables, has not violated the inclusion or exclusion criteria, has completed all trials and assessments, and was in good adherence. Second, we plan to compare the impacts of different statistical methods (i.e., stratified chi-square test and modified Poisson regression model) on the consistency of the primary outcome. Stratified chi-square analysis adjusted for major potential confounders, i.e., age, sex, use of steroids (yes/no), preoperative pain score, and long-term use of analgesics (yes/no) before surgery. Adjusted OR values will be calculated using the Cochran–Mantel–Haenszel test (CMH).

Secondary outcomes will be exploratory, without adjustment for multiple comparisons. The first time to enter the pain cycle within the first 24 postoperative hours and the first time to rebound pain within the first 24 postoperative hours will constitute the survival data. Kaplan–Meier survival curves and log-rank tests will be used to analyze survival data, and univariate COX regression will be used to calculate HR and 95% CI. NRS and opioid use at different postoperative intervals will constitute repeated-measurement data. Generalized estimation equation (GEE) will be used, with patient identification number as the main variable, time as the main internal variable, and NRS and opioid consumption as the dependent variables. Independent samples *t*-tests or Mann–Whitney U tests will be used to compare independent data between the groups. The Hodges–Lehmann method will be used to evaluate the pseudo-median differences and 95% CI. Categorical data will be expressed as the number of cases (percentage) and analyzed using the chi-square test, Yate’s chi-square test, or Fisher’s exact probability test. Safety outcomes will be analyzed using the safety analysis dataset. All participants who undergo randomization and for whom post-trial safety evaluation data are available will be included in the safety analysis dataset. All statistical tests will be two-sided and *p* < 0.05 will be considered statistically significant.

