### Sample size calculation

2.6.

The sample size was calculated based on the primary outcome. According to previous studies, the incidence of severe postoperative pain in patients undergoing TKA with multimodal analgesia is 25–40% (16, 17). Considering variance in multimodal analgesia and follow-up times, we reviewed the records of 20 patients who had undergone unilateral TKA in the past month. With multimodal analgesia, 48% of patients reported severe pain (NRS ≥ 7 points) within 12 postoperative hours. Therefore, we assumed that the incidence of rebound pain in patients undergoing TKA in the context of multimodal analgesia is 45%. We expect that the incidence of rebound pain in the esketamine group will be at least 35% lower than in the placebo group during the first 12 post-surgical hours. Using Power Analysis and Sample Size version 15.0 (Stata Corp. LP, College Station, TX, United States) and assuming a significance (*α*) level = 0.05 and power (1 − *β*) = 80% determined sample sizes for the esketamine group (*N*_1_) = 160 and placebo group (*N*_2_) = 160. Considering potential withdrawal (10%), a final 356 patients (178 in each group) will be included to achieve the appropriate power to test our hypothesis.

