### Double blinding

2.8.

This study will follow a double-blind design. According to the allocation protocol, participants will be randomized to receive a continuous infusion of esketamine or 0.9% normal saline during the operation. To ensure investigator blinding, the drug administrator ([name]) will prepare syringes (Weigao Group Medical Polymer Products Co., Ltd., Weihai, Shandong, China) in a separate room, labeling them A or B. One syringe will be filled with 50 mg of esketamine and 0.9% of normal saline (20 ml total) and the other will be filled with the same volume of 0.9% normal saline. The appearances of syringes A and B will be identical, other than label. The drug administrator will be unaware of the distribution plan and the intervention measures accepted by the participants. Because esketamine has sedative and hypnotic effects, to prevent unblinding the investigators and participants, all participants will be given preoperative 0.05 mg/kg intravenous midazolam. Throughout data collection, nurses, surgeons, outcome assessors, and statistical analysts will all be unaware of participant treatment group assignments. An independent data and safety supervision committee will monitor the trial, without disclosing participant grouping, until completion of statistical analyzes.

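### Section 7 plans three models for the primary outcome without naming the decisive one, and Model 3 adjusts for intraoperative variables recorded after randomisation

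*Protocol article*

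**What the plan says.** Section 7 (Statistical methods) of the protocol article plans three modified Poisson models for the primary outcome. Model 1 is unadjusted. Model 2 uses baseline variables only: sex, age, BMI, ASA grade, complications, long-term analgesic use and baseline pain. For the third, "model 3 will be adjusted for tourniquet use time, operation time, steroid use (yes/no) and analgesic and sedative doses during the operation". The text does not say which model gives the primary RR and p-value, nor whether Model 3 adds to Model 2 or replaces it.

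The sensitivity analyses come afterwards and separately: intention-to-treat against per-protocol, and modified Poisson against a stratified chi-square analysis. The latter uses the Cochran–Mantel–Haenszel (CMH) method, reports an odds ratio (OR), and adjusts for what the article calls major potential confounders: "age, sex, use of steroids (yes/no), preoperative pain score, and long-term use of analgesics (yes/no) before surgery".

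Timing is given elsewhere. Table 1 puts randomisation at Visit 1, one day before surgery, and the intervention at Visit 2. Section 4 lists every Model 3 covariate, steroid use included, among the intraoperative data. Section 2.12 runs the infusion from the end of spinal anaesthesia to suture and lets the anaesthesiologist choose other medication, apart from other NMDA antagonists. On the drug itself, section 2.8 justifies masking "Because esketamine has sedative and hypnotic effects", and section 2.12 also credits the chosen dose with analgesic effects.

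**The concern.** Randomisation makes the arms comparable on everything fixed before it. Models 1 and 2 keep that protection. Model 3 conditions on variables that arise later, and some of them could be consequences of treatment. If a sedating, analgesic study drug leads the anaesthesiologist to give less of other sedatives or analgesics, two things follow:

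- Where the dose itself affects later pain, adjusting for it removes part of the treatment effect.
- Where dose also reflects the patient's unmeasured pain sensitivity, patients at equal dose in the two arms are no longer comparable.

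Steroid use in the CMH analysis is a smaller instance. A variable arising after randomisation cannot confound the randomised comparison.

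With three models and no rule for precedence, the trial could report discordant RRs for its one confirmatory question, with nothing in the document to say which decides.

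**Working it through.** **Inputs from the documents.** Placebo rate: "we assumed that the incidence of rebound pain in patients undergoing TKA in the context of multimodal analgesia is 45" per cent (section 2.6). Reduction 35%, alpha 0.05, power 80%, 160 per group, 10% withdrawal (section 2.6). "All statistical tests will be two-sided" (section 7).

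**Step 1: reproduce the plan's sample size.** Read as relative, the esketamine rate is 0.45 × 0.65 = 0.2925, the difference is 0.1575 and the mean rate is 0.37125.

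- Pooled formula: n = [1.96·√(2 × 0.37125 × 0.62875) + 0.8416·√(0.45 × 0.55 + 0.2925 × 0.7075)]² / 0.1575² ≈ 146.5, so 147 per arm.
- With continuity correction: (146.5/4)·[1 + √(1 + 4/(146.5 × 0.1575))]² ≈ 159, which matches the stated 160.
- An absolute reduction of 35 points would need only 25 per arm, so the relative reading is intended and the planned RR is 0.65.
- Withdrawal: 160/0.90 = 177.8, so 178.
- Power with 160 per arm, uncorrected pooled formula: 83.4%.

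**Step 2: effect of Model 3, by simulation.** Each scenario had 3,000 trials of 320 patients, analysed by modified Poisson regression with robust standard errors. The outcome was generated on the logit scale, calibrated to 45% on placebo and to the stated true RR. Assumptions not in the documents: esketamine's effect on intraoperative dose (0 to −1 SD); correlation of dose with latent pain sensitivity 0.5; log-odds of 0.8 per SD of sensitivity. Model 3 contained the dose and three unrelated covariates.

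| Fall in dose (SD) | Model 3 RR, truth 0.65 | Model 3 power | Model 3 RR, truth 1.00 | Model 3 rejections under null |
|---|---|---|---|---|
| 0 | 0.65 | 84% | 1.00 | 4.8% |
| 0.25 | 0.69 | 70% | 1.05 | 7.0% |
| 0.5 | 0.72 | 55% | 1.10 | 11.4% |
| 1 | 0.80 | 24% | 1.21 | 28.3% |

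In all these scenarios Models 1 and 2 averaged RR 0.65 or 1.00, with power 82–83% and rejection 4.6–5.2% under the null.

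Variations at a 0.5 SD fall:

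- Correlation 0.3: RR 0.69 for a truth of 0.65, power 66%.
- Dose as a pure mediator (log-odds 0.5 per SD, no latent sensitivity): RR 0.75, power 47%.

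**Step 3: choosing among the models.** With no dose effect, the chance under the null that at least one of the three gives p < 0.05 was 6.3%. A run with seven baseline and five intraoperative covariates gave 6.9%. The independence bound, 1 − 0.95³ = 14.3%, does not apply because the models are highly correlated. With the dose falls in the table, the any-model rate was 9.2%, 13.8% and 31.2%. However, the rate of any model falsely showing benefit stayed at 2.8–2.9%, near the nominal 2.5%. The excess rejections point towards harm.

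**Step 4: scale of the CMH estimate.** OR = (0.2925/0.7075)/(0.45/0.55) = 0.413/0.818 = 0.51, against an RR of 0.65 for the same two rates.

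**The case against.** This is a condensed article, and naming the decisive model is often left to an analysis plan that is not shown. Model 1 is listed first and the sample size uses no covariates, so it could be taken as the implied primary. There may also be little room for a dose shift: surgery is under spinal anaesthesia plus adductor canal block, midazolam is set at the same mg/kg dose in both arms, and the specified fentanyl rescue is in the PACU. No text links esketamine to steroid use, tourniquet time or operation time.

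Much of this stands, and it limits the size of the point. It does not remove it: the article itself fixes Model 3's covariates and the steroid factor and sets three models side by side, and section 2.12 leaves other medication discretionary.

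A reader might infer more than the documents support:

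- **That Model 3 is biased.** Only if esketamine changes the doses, and the documents give no figure for that.
- **That free choice among models inflates false claims of efficacy.** Step 3 shows hardly any such inflation in the scenarios run. No text says that significance in any one model counts as success.
- **That the covariate nearly duplicates the arm because esketamine is itself a sedative dose.** Nothing says the study drug is counted among the covariates.
- **That the CMH analysis is unsound.** It is a labelled sensitivity analysis, only one of its five factors is intraoperative, and the OR is correctly named. Consistency can be judged on direction and significance.

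**Conclusion.** The point holds as a should-fix. Section 7 names no decisive model for the primary outcome, and Model 3 need not estimate the randomised effect because it conditions on variables recorded after randomisation. Intraoperative analgesic and sedative doses are the real risk; operation and tourniquet time are less likely to be affected by the drug.

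The size is conditional. It is nil if esketamine leaves the doses unchanged. Within the assumed 0.25–1 SD fall, Model 3 understates a true benefit and loses between roughly 12 and 58 percentage points of power (82% to 70% or 24%). A rise in dose would push the estimate the other way. The practical danger under a fall is therefore an attenuated or discordant Model 3 result with no rule to settle it, rather than a false claim for esketamine. Multiplicity from model choice alone is small, at about 6–7%.

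**What to change.** In section 7:

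1. Name one primary model without post-randomisation covariates, and label the other supportive. Model 1 and baseline-adjusted Model 2 are both valid; the choice is the sponsor's.
2. Delete Model 3, or label it exploratory and state that it is not an estimate of the treatment effect.
3. Remove intraoperative steroid use from the CMH factors.
4. Optionally, report a Mantel–Haenszel risk ratio there, so that the check is on the same scale as the primary RR.

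The cost is wording, made before unblinding. The sample size stays at 160 per arm, 178 after withdrawal. With Model 1 or Model 2 as primary, simulated type I error across all scenarios is 4.6–5.3% and power is 82–83%.

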### Primary outcome

3.1.

The primary trial outcome is incidence of rebound pain within the first 12 postoperative hours in the esketamine and placebo groups. Herein, rebound pain is defined as the transition from well-controlled pain (NRS ≤ 3) to severe pain (NRS ≥ 7) in participants undergoing TKA under regional block anesthesia.

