### Secondary outcomes

3.2.

Incidence of rebound pain within the first 24 postoperative hours.Time to entering the first pain cycle during the first 24 postoperative hours (i.e., time from PACU transfer to initial analgesic intervention).Time to first rebound pain during the first 24 postoperative hours (i.e., time from PACU transfer to first NRS ≥ 7).The modified rebound pain score (MRPS). MRPS = HNRS−LoNRS (PACU) (2), where HNRS (24) is the highest NRS pain score within 24 h after regional nerve block, and LoNRS (PACU) is the lowest NRS pain score while in the PACU.NRS scores at rest (i.e., laying quietly) and exercise (i.e., raising the affected limb ≥5 times to ≥30 cm) at: 1 day before their operation, PACU transfer, the morning of the first postoperative day; during physical therapy on the first postoperative day; the evening of the first postoperative day; the morning of the second postoperative day; and the evening of the second postoperative day. Morning is defined as 8–10 a.m. and evening as 8–10 p.m.The cumulative opioids upon transfer to the PACU and at 12, 24, and 48 postoperative hours. Cumulative opioids includes administration of basic and remedial analgesics, which will be converted to ‘morphine-equivalent dose’ for analyzes.One day before their operation and first postoperative Timed Up and Go test (i.e., time required to stand up from a standard-height armchair, walk forward three meters, walk back to the chair, and sit down).Range of motion [i.e., degree of the affected knee joint from neutral (0°) to maximum flexion] of the active and passive knee joints at 1 day before their operation and on the first postoperative day.Time to discharge (i.e., when the participant can walk from bed to bathroom independently and along the corridor without the help of a walker).Length of stay (i.e., number of days from admission to discharge).Quality of Recover (QOR)-15 scores at 1 day before their operation and the first postoperative day.Blood glucose and cortisol concentration at admission and the first postoperative day.Patient satisfaction at discharge, where 1 point is ‘unsatisfactory’, 2 points is ‘relatively satisfactory’, and 3 points is ‘satisfactory’.

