Patient satisfaction at discharge	–	–	–	–	–	–	X
Safety outcomes	Throughout the study period, until patient discharge						

NRS, numeric rating scales; POD, postoperative day.

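### The per-protocol check of the 12 h primary outcome excludes participants for assessments missed after 12 h, so it can differ from intention-to-treat for reasons unrelated to adherence

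*Protocol article*

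**What the plan says.** The Primary outcome section (3.1) defines the endpoint as the "incidence of rebound pain within the first 12 postoperative hours in the esketamine and placebo groups". Statistical methods (section 7) makes intention-to-treat the main analysis, with "data from all the participants assigned to randomized grouping, regardless of intervention, in a intention-to-treat analysis". A sensitivity analysis follows: "The effects of the intention-to-treat set and the per-protocol set on the consistency of the primary outcome will be compared". To enter the per-protocol set a participant must have complete main baseline variables and must also be someone who "has not violated the inclusion or exclusion criteria, has completed all trials and assessments, and was in good adherence".

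That condition has no time window and is not limited to the pain diary. Section 3.2 and Table 1 place many assessments after 12 h:

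- **Postoperative day 1:** the Timed Up and Go test ("time required to stand up from a standard-height armchair, walk forward three meters, walk back to the chair, and sit down"), active and passive range of motion, QoR-15 (listed in section 3.2 only), glucose and cortisol, and pain scores including one during physical therapy.
- **Postoperative day 2:** pain scores on "the morning of the second postoperative day; and the evening of the second postoperative day", at rest and on exercise, the latter meaning "raising the affected limb ≥5 times to ≥30 cm".
- **Discharge visit:** "Patient satisfaction at discharge".

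**The concern.** The endpoint is fixed at 12 h, but membership of the set that checks it is decided by what happens up to discharge. Someone who received the allocated infusion as planned and kept a full 12 h diary leaves the set for missing a walking test the next day.

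The protocol gives reasons why such misses might not be random. The Introduction says rebound pain harms sleep and rehabilitation, and several later assessments require effort with the operated leg. Drop-out criteria (2.4) counts no longer accepting assessments as withdrawal. Missing data handling (7.1) names side effects as a cause of missing data. Membership may therefore depend on the outcome being checked, on treatment, or on both.

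What is at stake is how the check is read. If the two sets disagree, or the per-protocol estimate looks stronger, a reader would put it down to adherence when it might reflect missed later assessments.

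**Working it through.** **Inputs from the protocol (section 2.6).** Placebo rate 45%; esketamine at least 35% lower; two-sided alpha 0.05; power 80%; 160 per group, raised to 178 for 10% withdrawal.

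**Reproducing the plan's figure.** Reading 35% as relative gives 0.45 × 0.65 = 0.2925, a relative risk (RR) of 0.65. The two-proportion formula with continuity correction gives 159 per group against 160 stated; without correction it gives 147. An absolute reading would need only 25 to 30 per group, so the relative reading is the one used. 160 / 0.90 = 177.8, rounded up to 178. None of this depends on the per-protocol definition.

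**Effect of selection.** Let p be the true rate in an arm, c1 the probability of completing all later assessments with rebound pain, and c0 the same without. Among those retained:

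rate = p·c1 / [p·c1 + (1 − p)·c0]

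Equivalently, the odds of rebound pain are multiplied by c1/c0. The odds ratio between arms is therefore distorted only by the ratio of c1/c0 on esketamine to c1/c0 on placebo. If that ratio is 1, the odds ratio is unchanged and the RR moves only because the rates are lower.

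**Assumed completion, since the documents give none.** Take c0 = 95% and c1 = 80% in both arms.

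- Placebo: 0.45 × 0.80 = 0.360; 0.55 × 0.95 = 0.5225; rate 0.360 / 0.8825 = 40.8%; retained 0.8825 × 178 = 157.
- Esketamine at 29.25%: 0.2925 × 0.80 = 0.234; 0.7075 × 0.95 = 0.672; rate 0.234 / 0.906 = 25.8%; retained 0.906 × 178 = 161.
- RR 25.8 / 40.8 = 0.63 against a true 0.65. With no true effect both arms read 40.8% and the RR is 1.00.

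**Varying c1 by arm, c0 = 95% throughout.**

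| c1 esketamine / placebo | RR when truth is 1.00 | RR when truth is 0.65 |
|---|---|---|
| 80% / 80% | 1.00 | 0.63 |
| 70% / 70% | 1.00 | 0.62 |
| 85% / 95% | 0.94 | 0.60 |
| 95% / 85% | 1.06 | 0.69 |
| 70% / 95% | 0.84 | 0.52 |
| 95% / 70% | 1.20 | 0.78 |

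**Side effects acting on everyone in the esketamine arm.** Start from 95%/80% in both arms and no true effect. If side effects cut esketamine completion in the same proportion with and without rebound pain (0.80 to 0.72 and 0.95 to 0.855), the factor cancels and the RR is 1.00. If they cut it by equal points, c1/c0 of 0.72/0.87 gives 40.4% / 40.8% = 0.99, and 0.65/0.80 gives 39.9% / 40.8% = 0.98.

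**The case against.** The main analysis is intention-to-treat in all randomized participants, with multiple imputation, and a missed later item does not remove an observed 12 h outcome from it. No success criterion rests on the per-protocol set, and every per-protocol set is selected after randomization. All of this stands, and it limits the consequence to the check itself.

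A reader might infer that the rule favours esketamine, because side effects would remove its patients. The documents do not support this. If side effects lower completion in only those esketamine patients who also have rebound pain (c1 of 72% or 65% against 80% on placebo, c0 unchanged), a null RR reads 0.94 or 0.88. No reason is given why side effects would spare patients without rebound pain. When they act on both subgroups, the RR stays between 0.98 and 1.00. Stronger dependence on placebo pushes the RR the other way.

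A reader might also take it as established that rebound pain causes missed assessments. The Introduction says it harms rehabilitation, not that tests will be missed, and blood samples and a satisfaction rating need no walking. The link is plausible and its size unknown.

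Finally, the pre-lock meeting in Data management (section 5) confirms how datasets are divided, and a fuller protocol may give detail. But the article states a rule, and that meeting would be expected to apply it.

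**Conclusion.** The concern holds as a defect in the definition of a sensitivity set. As written, participants can be excluded from the 12 h check for items missed after the endpoint is complete, so the check can differ from intention-to-treat for reasons unrelated to adherence. That reachability of later items follows from reading the condition together with Table 1; the sentence itself does not mention discharge.

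The size rests wholly on assumed completion rates. With dependence on rebound pain alike in both arms there is no bias under the null, and 0.65 moves only to about 0.62–0.63 at 70–80% completion with rebound pain. Bias becomes material only if that dependence differs by arm. In the cases shown, a null RR then reads 0.84 to 0.94, or 1.06 to 1.20 in reverse. Neither direction can be predicted from the documents. The primary estimate and the planned 178 per group stand.

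**What to change.** In section 7, for the per-protocol check of the primary outcome, replace the requirement to complete every trial and assessment with the requirement of a usable 0–12 h pain diary. Keep the eligibility, baseline and adherence conditions, judged on events up to 12 h. Add that assessments missed after 12 h do not exclude a participant from this set.

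The cost is one amended sentence before database lock. It needs no new data and leaves the sample size alone. Dropping the later-assessment requirement can only enlarge the set, and it removes selection on post-endpoint completion whatever the true completion rates are.

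### The method-consistency check on the primary outcome sets a relative risk beside an odds ratio on different covariates, so it can compare direction and significance but not effect size (minor)

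*Protocol article*

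**What the plan says.** All of this is in the protocol article, section 7 (Statistical methods), unless stated otherwise.

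- **Primary estimate.** For rebound pain within 12 h, "the relative risk (RR) and 95% confidence interval (CI) will be calculated using the modified Poisson regression model". Model 1 is unadjusted. Model 2 adjusts for gender, age, BMI, ASA grade, complications, long-term analgesic use and baseline pain. Model 3 lists tourniquet time, operation time, steroid use and intraoperative analgesic and sedative doses.
- **Second sensitivity analysis.** After an intention-to-treat versus per-protocol comparison, the plan is to "compare the impacts of different statistical methods (i.e., stratified chi-square test and modified Poisson regression model) on the consistency of the primary outcome".
- **The comparator.** The stratified analysis adjusts for age, sex, steroid use, preoperative pain score and long-term analgesic use. Its output is fixed: "Adjusted OR values will be calculated using the Cochran–Mantel–Haenszel test (CMH").
- **Criterion.** The text does not say whether consistency refers to the size of the estimate, its direction or its significance.
- **Timing of steroid use.** Section 4 (Data collection) lists steroid use among the intraoperative data. Table 1 places randomisation at Visit 1, the day before surgery.

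**The concern.** The two halves of one consistency check report different effect measures. When the outcome is common, the OR from a given table lies further from 1 than the RR from the same table, however well either analysis is done. Here the outcome is expected in nearly half of the placebo group.

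The adjustment set changes as well. Model 1 has no covariates. Model 2 has no steroid term and adds BMI, ASA grade and complications. Model 3 as written has only intraoperative items. If model 3 is meant to be added to model 2, the stratified set is a subset of it but still not equal to it.

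What is at stake is how the sensitivity result is read. With the two numbers printed side by side, a reader may call them inconsistent when they agree, or quote the stronger-looking OR as the size of the benefit.

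**Working it through.** **Inputs (section 2.6, Sample size calculation, and section 7).** Placebo incidence: "we assumed that the incidence of rebound pain in patients undergoing TKA in the context of multimodal analgesia is 45" per cent. Effect: "incidence of rebound pain in the esketamine group will be at least 35% lower than in the placebo group". Error rates: "assuming a significance (*α*) level = 0.05" and "power (1 − *β*) = 80" per cent. Sidedness: "All statistical tests will be two-sided". Stated size: 160 per group, 178 after 10% withdrawal.

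**Step 1: reproduce the stated sample size, which settles how the 35% is meant.**
- Relative reading: p1 = 0.65 × 0.45 = 0.2925. The two-sided normal formula for two proportions gives 147 per group without continuity correction and 159 with it, against the stated 160. Then 160 / 0.90 = 177.8, so 178.
- Absolute reading (45% to 10%): two-sided, 25 per group, or 30 with the correction. This does not fit.

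The design effect is therefore RR 0.65, with incidences of 45% and 29.25%.

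**Step 2: RR and OR from the same counts.** OR = RR × (1 − p0)/(1 − p1).
- RR = 0.2925/0.45 = 0.65.
- OR = (0.2925/0.7075)/(0.45/0.55) = 0.505.
- OR/RR = 0.55/0.7075 = 0.777, so the OR is about 22% below the RR.

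**Step 3: intervals with 160 per group, Wald on the log scale.**
- SE(log RR) = √[0.7075/(160 × 0.2925) + 0.55/(160 × 0.45)] = √(0.01512 + 0.00764) = 0.151. RR 0.65 (0.48 to 0.87), z = −2.86.
- SE(log OR) = √[1/(160 × 0.2925 × 0.7075) + 1/(160 × 0.45 × 0.55)] = √(0.03020 + 0.02525) = 0.235. OR 0.51 (0.32 to 0.80), z = −2.90.

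**Step 4: how the gap moves.**

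| Placebo incidence | RR | OR |
|---|---|---|
| 25% (low end of the range cited in 2.6) | 0.65 | 0.58 |
| 40% (high end) | 0.65 | 0.53 |
| 45% (design) | 0.65 | 0.51 |
| 48% (the centre's record review) | 0.65 | 0.49 |
| 45% | 0.80 | 0.69 |
| 45% | 1.00 | 1.00 |

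The gap depends on the effect and the incidence. It vanishes only when there is no effect.

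**Step 5: what the check can still do.** 1,000 trials of 356 patients were simulated with five binary stratification factors, whose prevalences and effects are assumed.
- With true RR 0.65, the median Mantel-Haenszel OR was 0.49 and the median adjusted Poisson RR 0.65. The direction matched that of the unadjusted Poisson model in 100% of trials. The significance verdict matched in 95% (Poisson on the same covariates) and 94% (unadjusted Poisson).
- With true RR 1.0, the significance verdicts matched in 96 to 97%.

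**The case against.** The best defence is that the plan names a stratified chi-square *test* as the comparator and never requires equal point estimates. RR and OR share the null value 1, so direction and significance compare directly. At the design rates the z values almost coincide, and the simulated verdicts agree nearly as often under the planned effect as under none. That stands. A reader might infer that the check cannot show robustness at all, but the documents do not support so strong a reading.

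A reader might also infer that stratifying on age and pain score leaves strata too thin to use. The document gives no categories, and cut-points are ordinary detail for an analysis plan that is not shown. With binary factors the simulated stratified test rejected in 85.5% of trials, against 86.7% for the unadjusted Poisson model, so the analysis is workable.

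The defence can add that covariate choice matters little to the verdict in a 1:1 randomised trial, that the output is openly labelled an OR, and that no stated decision hangs on it. These points lower the priority. They do not make the sizes comparable: the plan itself reports the primary result as an RR with an interval and fixes an OR as its counterpart.

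**Conclusion.** The point holds in a limited form. As written, the second sensitivity analysis can check whether the two methods agree on direction and significance. It cannot check whether they agree on effect size: at the planned rates it would set 0.65 beside about 0.51, an apparent 49% reduction beside a 35% one, from the same data. Because method, scale and covariates change together, a difference in size cannot be assigned to any one of them.

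The RR–OR gap uses only the protocol's own incidence and effect, with the 35% read as relative, as the stated sample size requires. The agreement percentages rest on assumed covariate distributions. The primary RR analysis and the sample size are unaffected. Priority: minor.

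**What to change.** Amend the end of the sensitivity-analysis text in section 7 as follows.

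1. Report the Mantel-Haenszel common relative risk with its 95% CI from the stratified tables, in place of the OR or beside it. With a_k and c_k the events and n1_k and n0_k the patients on esketamine and placebo in stratum k of size N_k, RR = Σ(a_k n0_k/N_k) / Σ(c_k n1_k/N_k).
2. Fit one modified Poisson model on exactly the same covariates, in the same categories, and name it as the counterpart.
3. Limit both to variables fixed before randomisation: age, sex, preoperative pain score and long-term analgesic use. Leave steroid use out of this pair, since it is recorded during surgery and after allocation.

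The two RRs then differ only in method. If the OR is kept, say that it is compared on direction and significance only.

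The cost is one or two sentences, a small extra calculation and no new data. The sensitivity estimate will also look less extreme, about 0.65 rather than 0.51 at the design effect.
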